## 6.7 ANALYSIS OF SECONDARY OUTCOMES

For all secondary outcomes the continuous variables will be analysed using multi-level (mixed effect) linear regression models and categorical (binary) measures will be analysed using multi-level (mixed) logistic regression models. The secondary models will follow the same structure as the primary, including Stratification variables (Site) as

a random effect along with gender, age (continuous), years of education (continuous) and RBANS composite score at baseline as fixed factors and baseline score of the outcome to account for baseline differences. Unadjusted (section 6.5) and adjusted results will be presented with associated 95% confidence intervals.

Appendix 1 details all outcomes for the trial, variable types and their corresponding analysis.

## **6.8 SUBGROUP ANALYSES**

Subgroup analysis of “responders” and “non-responders” will be run by presenting demographic data and baseline scores for the two groups (responder vs non-responders) to explore if response can be predicted.

“Responders” will be defined as scoring at least 2 points difference from baseline in goal attainment rating measured on the BGSi (primary outcome) at each timepoint respectively.

This will also be carried out for those that significantly surpass the 2-point improvement defined as those who achieve 4 or more points difference at follow up compared to baseline.

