## 6 Statistical analysis

Primary analysis of the BGSi will be completed on an ITT basis at the 3 month endpoint using mixed effect models. Stratification variables will be incorporated into the model and other potential factors that could affect the results will be determined a priori and considered for inclusion in the models. All treatment effect estimates will be presented with 95% confidence intervals and 5% level of significance will be used. Analysis of secondary outcomes will follow the same analysis model as the primary analysis where possible. Binary outcomes will be analysed using multi-level logistic regression. Exploratory analysis will be conducted to investigate the effect of phenotypes and comorbidities on the outcome.

Where possible missing data will be minimised however a maximum-likelihood multiple imputation approach will be used with a sensitivity comparison of complete case dataset. The planned analysis will be specified in the statistical analysis plan (SAP), any deviations from the analysis plan will be justified and fully documented in the results report.

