### 7.1 Power calculation

Evidence from the GREAT trial of cognitive rehabilitation in neurodegenerative disease using the same primary outcome Bangor Goal Setting Interview (BGSi) indicated an effect of approximately 0.8 in a population with dementia. This is likely to be an underestimation of the effect in this study as it is likely that the intervention will be more effective in people without neurodegeneration as seen in the population in the GREAT trial.

Assuming a minimally clinically important difference of 2 points (<https://www.thecopm.ca/faq/>) and a more conservative effect of 0.7 would require SD of the measure to be approximately 2.86. Baseline SD observed in the GREAT trial was 1.74, it is likely that variability in our sample is likely to be larger and therefore we can accommodate an Increase in variability of approximately 65%.

A sample of 88 (44:44) will be required to detect an effect of 0.7 on the BGSi at 3 months with 90% power at a 5% significance level. Incorporating an attrition of 25% will require recruitment and randomisation of 118 participants (59:59).

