| BANGOR GOAL SETTING INTERVIEW                                                                                                                                                                                                                                                                                                                                                                                                | 
Each scored on a scale from 1 – 10.
 
Variables in dataset:
Attainment
Goal %
Satisfaction
Generalisation
                                              | 
mean attainment score will be calculated.
 
 
Mean Attainment Score = Sum of attainment scores (goal 1, goal 2, goal 3) / number of goals set (3)
 
 
Scores range from 0 – 10.
                                                                                                              | N/A                                                                                 | N/A                                                                                                                                                                                   | N/A | Higher scores indicate better goal attainment and satisfaction |

|  |                                       |                                                                                                                                                                                                                                                                                                                                                                                                                                                                                                                                                       |  |  |  |  |
|--|---------------------------------------|-------------------------------------------------------------------------------------------------------------------------------------------------------------------------------------------------------------------------------------------------------------------------------------------------------------------------------------------------------------------------------------------------------------------------------------------------------------------------------------------------------------------------------------------------------|--|--|--|--|

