|  | Readiness
Importance
difficulty | 
Using mean scores calculated, attainment change scores can also be calculated:
 
 
• Change 1 = T1 mean score – Baseline mean score
 
• Change 2 = T2 mean score – Baseline mean score
 
• Change 3 = T2 mean score – T1 mean score
 
 
Goal satisfaction scores will be calculated:
 
 
• Mean Satisfaction score = Sum of attainment scores (goal 1, goal 2, goal 3) / number of goals set (3)
 
 
Scores range from 0 – 10.
 |  |  |  |  |
|--|---------------------------------------|-------------------------------------------------------------------------------------------------------------------------------------------------------------------------------------------------------------------------------------------------------------------------------------------------------------------------------------------------------------------------------------------------------------------------------------------------------------------------------------------------------------------------------------------------------|--|--|--|--|

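### The responder table in SAP 6.8 groups participants by change from baseline and then reads baseline as a predictor, so low baseline attainment will usually look predictive even when it modifies nothing, and the table cannot show who benefits from treatment

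*Combined protocol and SAP*

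**What the plan says.** SAP 6.8 is headed as subgroup analysis. Responders are those "scoring at least 2 points difference from baseline in goal attainment rating measured on the BGSi", at each timepoint. A second, stricter group is "those who achieve 4 or more points difference at follow up compared to baseline". The analysis "will be run by presenting demographic data and baseline scores for the two groups (responder vs non-responders) to explore if response can be predicted". The section names no test, estimate, between-arm contrast or interaction, and does not say how participants without follow-up are classified.

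SAP Appendix 2 gives the change score: "Change 1 = T1 mean score – Baseline mean score". It also gives the item scale: "Each scored on a scale from 1 – 10". The mean score has the same upper limit of 10.

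Two other places bear on how 6.8 would be shown. SAP section 2 lists 6.8 among the further analyses of intervention data that follow unblinding. SAP 6.5 ends by saying that data are shown overall and by allocation group.

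Protocol section 6 promises: "Exploratory analysis will be conducted to investigate the effect of phenotypes and comorbidities on the outcome". The SAP has no such analysis. Section 6.9 deals with complete cases, sessions and time windows, and 6.10 with the BGSI readiness, importance and difficulty ratings.

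**The concern.** The grouping variable is follow-up minus baseline, and baseline is then inspected as a predictor of group membership. The two are linked by construction. Regression to the mean usually puts people with low baseline attainment among the responders, and the ceiling keeps people with high baseline attainment out. The same applies, more weakly, to any baseline score correlated with attainment.

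For demographics and other variables the difficulty is different. A pooled comparison of responders with non-responders mixes those who would have improved anyway with those whom treatment helped. The rehabilitation is tailored to cognitive profile, so readers will look to this section to learn who benefits, and the table cannot tell them. The 2-point threshold is also the minimally important difference behind the power calculation, yet no comparison of the proportions reaching it is specified.

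**Working it through.** **The plan's own figures.** Section 6.8 states none. The sample size inputs reproduce: a two-sided 5% test with 90% power for 0.7 SD needs 43.9 per arm by the t distribution, so 44 per arm and 88 in all. Then 88 / 0.75 = 117.3, so 118. The planning SD is 2 / 0.7 = 2.86.

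**Inputs.** From the documents: thresholds of 2 and 4 points (SAP 6.8); maximum 10 (SAP Appendix 2); a baseline SD for which protocol 7.1 says "Baseline SD observed in the GREAT trial was 1.74"; and the planning SD of 2.86 from the same section. Assumed, because the documents are silent: baseline mean 4; correlation r between baseline and follow-up of 0.3 to 0.7; follow-up SD of 2.0 or 2.86; a shift common to both arms of 0 or 1 point. The treatment effect is 0 or a constant, so baseline never modifies it.

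**Ceiling.** 10 − 2 = 8 and 10 − 4 = 6. A baseline mean above 8 can never be a 2-point responder, and one above 6 can never be a 4-point responder.

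**Sign of the link.** Cov(B, F − B) = SD_B × (r × SD_F − SD_B). This is negative when the slope r × SD_F / SD_B is below 1. With equal SDs, Corr(B, F − B) = −√((1 − r)/2), which is −0.59, −0.50 and −0.39 for r = 0.3, 0.5 and 0.7.

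**One case by hand**, ignoring the scale limits. Take SD 1.74 at both times, r = 0.5, no effect and no shift. The change SD is 1.74 × √(2 × 0.5) = 1.74, so z = 2 / 1.74 = 1.149, the responder share p is 0.125 and the normal density at z is 0.206. The baseline gap is 0.5 × 1.74 × (0.206/0.125 + 0.206/0.875) = about 1.64 points. Simulation with scores held to 1–10 gives 1.40, with 11.9% responders.

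**Range at the 2-point threshold** (simulated; gap is non-responder minus responder baseline mean):

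| SD baseline → follow-up | r | Slope | Gap, points |
|---|---|---|---|
| 1.74 → 2.0 | 0.3 to 0.7 | 0.34 to 0.80 | about 1.4 down to 0.5 |
| 2.86 → 2.86 | 0.3 to 0.7 | 0.30 to 0.70 | about 2.1 down to 1.2 |
| 1.74 → 2.86 | 0.3 | 0.49 | about 0.8 |
| 1.74 → 2.86 | 0.5 | 0.82 | about 0.3 |
| 1.74 → 2.86 | 0.6 | 0.99 | near 0 |
| 1.74 → 2.86 | 0.7 | 1.15 | about −0.3 |

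At the 4-point threshold with SDs 1.74 and 2.0 the gap is about 0.7 to 1.7 points.

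**How visible it would be.** With 88 participants and equal SDs (1.74 or 2.86), a t-test of baseline between the 2-point groups would give p < 0.05 in about 34% to 99% of trials, and in 74% to 94% at r = 0.5. Section 6.8 plans no such test; the figures show only how often the table would look persuasive.

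**Responders without treatment benefit.** With no treatment effect and SDs 1.74 and 2.0, 10% to 35% of each arm meet the 2-point definition. With a constant 2-point effect, SD 1.74 at both times, r = 0.5 and no shift, 11.9% of controls and 49.4% of the intervention arm do. That contrast carries the information about treatment, and 6.8 does not ask for it.

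**Splitting by arm.** Within the intervention arm alone, with SDs 1.74 and 2.0, the gap is still about 0.6 to 1.4 points.

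**The alternative.** With a constant 2-point effect and n = 88, an allocation-by-baseline interaction rejected in 3.9% to 5.7% of simulated trials, against a nominal 5%. Its power for two equal subgroups (four cells of 22, no covariate adjustment) uses SE = √(4/22) = 0.426 SD. For a 0.7 SD difference in effect, 0.7 / 0.426 − 1.96 = −0.32, so power is about 38%. For 1.4 SD it is about 91%.

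**The case against.** The strongest reply is that 6.8 is descriptive, aims only to explore prediction and claims nothing about treatment benefit, while 6.6 answers the between-arm question with adjustment for baseline BGSI. That is right about the consequence: no confirmatory result changes. It does not rescue the table, because prediction is what the coupling distorts.

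Four stronger readings are tempting, and the documents do not support them.

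- A reader might infer that the baseline gap is forced. It is not. It depends on the slope of follow-up on baseline, and it vanishes or reverses if the SD rises from 1.74 to 2.86 with r of 0.6 or more. The protocol does not say whether 2.86 applies at baseline, at follow-up or at both.
- A reader might infer that the arms will never be shown separately. SAP section 2 and the end of 6.5 leave open a display by arm or within the intervention arm. Either still conditions on the outcome, keeps the coupling and lacks an interaction.
- A reader might think the responder definition has no direction. The last paragraph of 6.8 calls the threshold an improvement, and Appendix 2 defines change as follow-up minus baseline with higher scores better.
- A reader might infer that 6.8 took the place of the protocol's phenotype and comorbidity analysis. The documents show only that the analysis is absent from the SAP. Its protocol wording could also be read as prognostic.

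**Conclusion.** The point holds as an improvement to an exploratory section. As written, 6.8 will usually present low baseline attainment as a predictor of response when it modifies nothing, and it cannot separate prognosis from treatment benefit.

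The direction is likely, not certain, and the size rests on an assumed baseline mean, correlation and follow-up SD. The artefact concerns baseline attainment and its correlates; for demographics the objection is only the missing between-arm contrast. The primary analysis is unaffected.

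**What to change.** In SAP 6.8:

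1. Report the proportion improving by at least 2 and at least 4 points in each arm at 3 and 6 months, with a covariate-adjusted risk difference and 95% CI. Handle missing follow-up by the rules of SAP 4.6, under which multiple imputation is conditional, and say how participants without follow-up are classified.
2. Replace the comparison of responders' and non-responders' baselines with exploratory treatment-by-baseline interactions in the 6.6 model. Use a short list fixed before unblinding, of measures already collected: for example RBANS composite, Chalder fatigue and PHQ-8. Report estimates with CIs.

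The second change also supplies the phenotype and comorbidity analysis promised in protocol section 6. A dysexecutive versus amnesic profile should be used only if a classification rule is written down beforehand, since the documents give none.

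The cost is SAP wording and a few extra models, with no new data. The responder proportions discard information that 6.6 already uses, so they supplement that model. The interactions have low power (about 38% for a 0.7 SD difference at n=88) and must be labelled exploratory, with no conclusion drawn from a non-significant result.

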## **6.9 SENSITIVITY ANALYSES OR MODEL TESTING**

If MI is used, then complete case analysis will be run to evaluate any impacts that MI has had on the results. This will be done on the primary outcome (BGSi attainment at 3 months) and any secondary outcomes that are statistically significant with MI analysis.

A sensitivity analysis will be run for the number of intervention sessions attended\*; this will be run by including number of sessions in the analysis model (as a continuous variable) along with the interaction with group.

An additional sensitivity analysis will be conducted on the primary outcome (BGSi attainment at 3 months) to assess impact of intervention treatment windows\*. Along with including number of sessions in the model as above, participants who did not receive the intervention within the correct window for any one session will be excluded (not including missed sessions).

*\*Presented in unblind report once all primary analysis listed in this SAP is complete.*

Sensitivity analysis will be conducted on the primary outcome (BGSi attainment score) at 2 and 6 months only including the participants whose data was collected within the aimed timeframe, that is within 2 weeks of the follow up due date.

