## 4.6 MISSING DATA

Every effort will be taken to minimise missing data. If imputation (e.g., mean substitution) is part of the validated measure it will be performed, see Appendix 1 for measure scoring rules. Where there are no missing data rules for the measure, if the number of missing items on an outcome is 20% or less, then the missing value for the item will be substituted by the individual's mean score for the remaining items on the scale (Bono, Ried, Kimberlin and Vogel 2007). If there are more than 20% missing items in the scale the outcome measure will not be calculated for the participant at that time point and multiple imputation methods will be used.

In accordance with the recommendations of Jakobsen, Gluud, Wetterslev and Winkel (2017), if the proportion of missing data is less than 5%, no imputation of missing data will be performed, and analyses will be based on complete cases. If the proportion of missing data is equal to or greater than 5%, a missing completely at random test devised by Little (1998) will be performed to assess whether the data is missing completely at random (MCAR). If this test indicates that data is missing completely at

random then analyses will be based on complete cases, else independent t-tests and Chi-square tests will be conducted to investigate whether the data is missing at random (MAR). If these tests suggest that the missing data is MAR, then predictive mean matching multiple imputation methods will be employed. Otherwise, additional modelling guided by clinical knowledge would be required to simulate the missing data mechanism and impute the missing data.

For multiple imputations, the number of imputations completed will be dependent upon the percentage of missing data (White et al., 2011). The missing outcome measures will be imputed using Allocation Group and Stratification factors (Site) and other variables that are deemed to be predictors of missingness. Variables will be assessed for being predictors of missingness by running statistical tests on completers versus non completers and evaluating if any differences are present between the two.

Variables to be assessed as predictors of missingness include;

- Age
- Sex
- Ethnicity
- Education
- Disability
- Occupation
- Drugs
- CV19 (diagnosed conditions (before/during))
- Number of vaccines
- Cognition

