If MI is used, complete case analysis will also be conducted as a sensitivity analysis to check the assumptions of the MI models, see section 6.8. In line with the recommendations of Jakobsen et al (2017), if more than 40% of data is missing for an outcome measure the data will not be imputed and an analysis will be conducted on complete cases, though the results of the analysis will be interpreted tentatively.

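### SAP 6.9 runs the complete-case check on an imputed secondary outcome only if the imputed result is significant, a limit that SAP 4.6 and protocol section 6 do not set

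*Combined protocol and SAP*

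**What the plan says.** Three places deal with the complete-case comparison.

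- Protocol section 6 plans that "a maximum-likelihood multiple imputation approach will be used with a sensitivity comparison of complete case dataset". It then leaves the detailed analysis to the SAP.
- SAP 4.6 states: "If MI is used, complete case analysis will also be conducted as a sensitivity analysis to check the assumptions of the MI models". For detail it sends the reader to SAP 6.8, which is the responder subgroup section and says nothing about complete cases.
- SAP 6.9 gives the purpose, namely that "complete case analysis will be run to evaluate any impacts that MI has had on the results". It then restricts the check to BGSI attainment at 3 months and "any secondary outcomes that are statistically significant with MI analysis".

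SAP 4.6 also fixes when MI is used at all. An outcome with under 5% missing, or with over 40% missing, is not imputed and is analysed on complete cases. Between those limits, data that pass the test for missing completely at random (MCAR) are also analysed on complete cases. MI is left for outcomes with 5 to 40% missing that are not judged MCAR.

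SAP 4.3 makes all tests two-sided at 5% and classes every secondary outcome as exploratory, without multiplicity adjustment.

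**The concern.** A sensitivity analysis should show how far a result depends on a modelling choice. That question is the same whether the p-value falls above or below 0.05. Under SAP 6.9, the decision to look is made after the imputed result is known. If MI gives significance and complete cases do not, the reader sees the disagreement. If complete cases give significance and MI does not, the adjusted complete-case model is never fitted and the outcome is reported as null with nothing beside it.

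The affected outcomes are those on which the plan relies for breadth: BGSI attainment at 6 months, goal satisfaction, and the function, mood, fatigue, sleep and post-exertional malaise scales. Because they are exploratory, they are better read by estimate and interval than by threshold, and a significance gate suits them poorly. The team also needs to know which of the two SAP sections to follow.

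**Working it through.** **1. The passages compared.** Take a secondary outcome that has been imputed and is not significant with MI.

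| Source | Is the complete-case model run? |
|---|---|
| Protocol section 6 | Yes; no limit stated |
| SAP 4.6 | Yes; no limit stated |
| SAP 6.8 (where 4.6 points) | Silent |
| SAP 6.9 | No |

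**2. Where the rule bites.** With under 5% missing, over 40% missing, or data judged MCAR, complete cases are already the main analysis and nothing is lost. The gap is confined to 5 to 40% missing and not judged MCAR. The attrition assumed for the sample size, 25%, lies in that range.

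**3. How many models.** From SAP Appendix 1, leaving out the cognitive batteries (their analysis is still to be confirmed) and the health-economic measures: BGSI attainment at 6 months (1), BGSI satisfaction at 3 and 6 months (2), and eight scales at two visits (8 × 2 = 16). The total is 1 + 2 + 16 = 19.

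**4. What the gate reveals.**

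| | Complete case significant | Complete case not significant |
|---|---|---|
| MI significant | checked, agree | checked, disagreement shown |
| MI not significant | not checked, disagreement not shown | not checked |

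The trigger is two-sided significance, so a significant worsening with MI is checked just as a significant improvement is.

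**5. Illustrative size.** The documents give no figure for such disagreement. The trial size used below does reproduce: for an effect of 0.7 at two-sided 5%, 44 per arm gives 90.1% power by the noncentral t distribution, and 88 / (1 − 0.25) = 117.3, rounded up to 118. Everything else in this step is assumed.

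Both simulations use 118 participants, about 25% of outcomes missing, predictive mean matching with 25 imputations pooled by Rubin's rules, and a baseline-adjusted linear model. Entries are the percentage of simulated trials.

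*Simulation A*: 1,500 trials per effect; missingness depends on an auxiliary variable; residual SD 0.75.

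| True effect (points) | Complete case only significant (not shown) | MI only significant (shown) |
|---|---|---|
| 0 | 0.8 | 1.5 |
| 0.2 | 2.9 | 3.1 |
| 0.3 | 3.5 | 4.7 |
| 0.4 | 3.9 | 5.0 |

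*Simulation B*: 2,000 trials per setting; standardised effect d.

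| Missingness | d | Complete case only significant (not shown) | MI only significant (shown) |
|---|---|---|---|
| MCAR | 0 | 0.8 | 0.5 |
| MCAR | 0.3 | 2.6 | 1.8 |
| MCAR | 0.5 | 2.6 | 1.5 |
| Auxiliary-driven, opposite in the two arms | 0 | 8.7 | 1.8 |
| Same | 0.3 | 0.2 | 22.7 |
| Same | 0.5 | 0.1 | 29.2 |

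The MCAR rows are a reference only, since SAP 4.6 would not impute such data. Over all settings the unshown disagreement runs from about 0.1% to 8.7%, driven mainly by the missingness mechanism. In the arm-opposed setting complete cases are biased. The 8.7% at d = 0 is therefore largely complete-case false positives rather than effects that MI concealed.

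**The case against.** The strongest reply is that this is general text followed by specific text. Neither SAP 4.6 nor the protocol says the check applies to every outcome; that is inferred from their lack of a limit. The protocol hands detail to the SAP. The pointer to 6.8 looks like a numbering slip for 6.9, and SAP 4.5 has a similar one, sending a sensitivity analysis to the descriptive section. On this reading, testing only those exploratory findings on which a claim might rest is a cautious choice made in advance. This stands in part. The texts can be reconciled that way, so a flat contradiction is not proved. But the restriction is missing from the section that 4.6 cites, and the gate still does not serve 6.9's stated purpose.

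A reader might go further and infer that the check can only weaken favourable results, or that a worsening would go unseen. The documents do not support either. Tests are two-sided, a complete-case result can confirm the MI result as well as undermine it, and SAP 6.5 and 6.7 present outcomes by arm with completeness levels and unadjusted results for all secondary outcomes. Those summaries do not replace the adjusted complete-case model, but a marked difference in the observed data would probably be visible.

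Finally, where MI is used the plan has already judged that the data are not MCAR. Significance in complete cases alone may then reflect complete-case bias. That limits what a disagreement proves, but it is no reason to show disagreements of one kind only.

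**Conclusion.** The point holds as a modest, cheap improvement. For imputed secondary outcomes, SAP 6.9 makes the adjusted complete-case model depend on the imputed p-value, while SAP 4.6 and protocol section 6 set no such condition. Results significant only with MI are exposed in either direction of effect; results significant only in complete cases are not.

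The primary inference is untouched, because BGSI attainment at 3 months is checked whenever it is imputed, and the secondary outcomes are exploratory.

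It is tempting to multiply a simulated percentage by the number of secondary tests and report how many disagreements would be hidden. The documents do not support this. They give no secondary effect sizes, no missingness mechanism and no auxiliary-variable strength. The simulated range of roughly 0.1 to 9% comes entirely from such assumptions. The simulations also use linear models only, whereas post-exertional malaise is analysed by logistic regression, and they count crossings of p = 0.05 rather than comparing estimates. They show that the unshown disagreement can occur, not how often it will in this trial.

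**What to change.** In SAP 6.9, replace the restriction with wording to this effect: where MI is used, the complete-case model will be fitted for the primary outcome and for every secondary outcome analysed with MI, irrespective of statistical significance. Add that MI and complete-case estimates will be tabulated side by side with 95% confidence intervals, and compared on size and precision rather than on which side of 0.05 each falls. In SAP 4.6, change the cross-reference from 6.8 to 6.9.

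Narrowing SAP 4.6 to match 6.9 would restore consistency but leave the check dependent on the result.

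The cost is up to 19 extra model runs outside the cognitive batteries, fewer if some outcomes need no imputation, plus a longer results table. No new data are needed, and the sample size does not change.
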